### Sample size {14}

It was estimated that a sample size of up to 375 total participants would be required to achieve study objectives. This estimate was informed by a sample size calculation. Figure 3 displays power and sample size estimates based on intervention effect sizes and covariates. Meta-analytic data from Finitsis et al. [44] of mHealth text messaging interventions to promote ART adherence among PLWH has shown that such interventions can improve VL suppression (*k* = 3; OR = 1.57, 95% CI = 1.11, 2.20). This OR of 1.56 is a small effect size, and Chen et al. [45] established conventions of small, medium, and large ORs (similar to Cohen’s magnitudes of effect size, *d*). Based on the Finitsis meta-analysis (OR = 1.57), and accounting for other possible effect sizes of small (OR = 1.68) or medium (OR = 3.47) magnitude (based on Chen et al.) [45], the required sample sizes to achieve adequate power of at least 0.85 ranges from *n* = 179 to 204; with covariates in the model (accounting for 25% of the variance in the outcome, then a sample size ranging from *n* = 263 to 339 would be required). To provide further support for this power analysis, we conducted another analysis in G*Power using an effect size estimate from a recent peer navigation intervention (that does not include a mHealth component, “LINK LA” [46]) for HIV-positive men and transgender women released from jail. In this study, the investigators tested the efficacy of their peer navigation intervention compared to usual care (case management) and found a 22% difference-in-difference between the intervention and control arm on viral suppression over a 12-month follow-up. Using this effect size information, and assuming 0.80 power, alpha = 0.05, and 1:1 allocation ratio between intervention and control arms, the required sample size is 97 per group, or a total *n* of 194. Altogether, our calculations to estimate the desired sample size with adequate power and, based on up to 20% anticipated attrition, a sample size between 225 and 375 would provide us with adequate power to achieve our aims. Thus, our goal is to randomize up to 375 participants for an analytic sample size of ~ 300 (150 per arm).

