The primary analytic approach will utilize generalized mixed-effects models and an intent-to-treat (ITT) approach. This addresses issues with attrition, missing data, and other unintended violations of design, thereby allowing us to maximize statistical power by not excluding subjects with some missing data. Mixed-effects models incorporate random intercepts and slopes for each participant based on the participant’s multiple measurements over time [65]. Intra-class correlations among participants nested within specific peer navigators will be examined to diagnose whether significant variation in outcomes is explained by the shared peer navigator, if so, models will account for clustering. Attrition analyses will compare participants who complete all measurements to those who do not based on baseline characteristics. If there is a baseline imbalance between participants retained in the study versus not across certain characteristics, then these will be accounted for in all analyses. In addition, maximum likelihood will be used to address incomplete data because this makes the relatively mild assumption that missing data are conditionally missing-at-random [66]. Outcome analysis will apply a priori planned comparisons. It is hypothesized that compared to control, participants in the PATH intervention will exhibit the following: greater viral suppression at 6- and 12-month follow-up (HYP 1); greater retention in care (HYP 2); fewer gaps in HIV care (HYP 3); greater ART adherence (HYP 4). HYP 1–3 involve binary outcomes (Y/N on sustained viral suppression, retained in care, had gaps in care), while HYP 4 is a continuous outcome (proportion). These hypotheses will be tested using regression analysis specifying the appropriate outcome distribution (e.g., binomial) and function (e.g., logit), with *α* = .05; any subsequent post-hoc comparisons will be adjusted via simulation-based stepdown methods [67] to maintain a nominal type 1 error rate of .05. For the primary outcome sustained viral suppression, we will assume non-suppression at that time point (6 or 12 months) for any missing viral load chart data. A sensitivity analysis will be conducted utilizing only available viral load chart data to compare with the results assuming missing viral load equals non-suppression.

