## Discussion

The PATH intervention integrates peer navigation and mHealth technology into a unified, scalable intervention that could both strengthen the impact of peer navigation on HIV care outcomes among PLWH, and simultaneously reduce the amount of implementation resources needed to support peer navigation in clinical settings. Not unlike other studies focused on marginalized populations, the challenge that we anticipated and have encountered thus far is with recruitment [70]. We originally aimed to recruit and enroll at least 15–16 new participants each month across 24 months. Instead, the enrollment rate on average has remained at a steady 11–12 new participants per month. By definition, the population from which we are trying to recruit are individuals who are poorly engaged in HIV care, or who are at risk of falling out of care. Additionally, the trial faced the unique factors associated with a trial launch during a global pandemic. Recruitment began in November 2021, during historically high rates of COVID-19 due to the Omicron variant [71]. Another historical factor affecting recruitment was the outbreak of MPOX in the summer of 2022 [72]. However, we believe that recruitment has been successful overall given the fact that it has continued at a consistent rate in the context of these unprecedented environmental challenges. Thus, in August 2023, the decision was made to extend the recruitment period to 30 months (+ 6 months).

Study retention and loss to follow-up are other factors of concern, since this is known to potentially lead to biased results in RCTs [73, 74]. As described in our analytic approach, we will account for any characteristics associated with loss to follow-up during analysis. Prior to that, we are making every effort to promote retention and minimize loss to follow-up, with the goal of maintaining at least 80% retention at each study visit. We expect to meet this threshold, owing in large part to the dedicated staff overseeing study retention. These staff are not only highly trained but are also employed by the community-based FQHC where the trial is being conducted, potentially minimizing any distrust of researchers that is often found especially in marginalized and racial/ethnic minority communities [75, 76].

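### The sample size takes 20% attrition off N with the effect intact, but the primary analysis keeps everyone and counts a missing viral load as failure, so the stated power does not belong to the primary test

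*Protocol article*

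**What the plan says.** The Sample size section ({14}) derives its target "based on up to 20% anticipated attrition". It concludes that "a sample size between 225 and 375 would provide us with adequate power to achieve our aims", and then that "our goal is to randomize up to 375 participants for an analytic sample size of ~ 300 (150 per arm". One of its two supporting calculations uses a cited peer-navigation trial that "found a 22% difference-in-difference between the intervention and control arm on viral suppression over a 12-month follow-up", "assuming 0.80 power, alpha = 0.05, and 1:1 allocation ratio between intervention and control arms". The other uses odds ratios of 1.57, 1.68 and 3.47.

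The Outcomes section ({12}) defines the primary outcome as a viral load below 200 copies/mL at both 6 and 12 months. The statistical methods section ({20a}) sets the rule for missing values of that outcome: "we will assume non-suppression at that time point (6 or 12 months) for any missing viral load chart data". An analysis restricted to available viral loads is named as a sensitivity analysis. Section {20c} analyses participants as randomised. Both sections also mention maximum likelihood for incomplete data, but the rule written specifically for the primary outcome is missing equals non-suppression.

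On expected completeness, the Discussion describes the retention effort "with the goal of maintaining at least 80% retention at each study visit". Section {18a} takes viral loads from the chart within 30 days of the due date and offers a laboratory draw when the chart has none.

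**The concern.** Attrition can enter a power calculation in two ways. Missing people can be dropped, giving a smaller N and the full effect. Or they can be kept and scored as failures, giving the full N and a smaller effect. The sample-size section does the first and the primary analysis does the second. The two do not give the same power. The two-visit outcome adds to the difference, because a missing value at either visit makes the composite a failure unless the other visit has already settled it.

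At stake is whether the statement of adequate power, especially at the lower end of 225 to 375, describes the test on which the trial will be judged.

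**Working it through.** **Reproducing the plan's figures.** 300 / 0.80 = 375, and 180 / 0.80 = 225. The attrition step is arithmetically correct. The issue is which analysis it describes.

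**Inputs from the protocol.** 375 and 225 randomised; 20% attrition; a 22-point difference; OR 1.57; alpha 0.05 (taken as two-sided); 1:1 allocation; suppression required at both visits; missing counted as failure.

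**Assumptions, because the document gives no figure.** Control sustained-suppression rate p of 40%, 50% or 60%. Share m of composites set to failure, equal in the two arms. The planning effect is the effect among observed participants, which is how the sample-size section uses it when it applies it to the 300 analysed.

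**Range for m.** If one loss covers both visits, 20% attrition gives m = 0.20. If 20% are missing independently at each visit, m = 1 - 0.8 x 0.8 = 0.36. I also show m = 0.10.

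**Formula.** Two-proportion z test with n per arm and control and intervention rates p and q. Let r = (p + q)/2, s0 = sqrt(2r(1-r)/n) and s1 = sqrt((p(1-p) + q(1-q))/n). Power = Phi((q - p - 1.96 s0)/s1). Under missing equals failure, replace p and q by p(1-m) and q(1-m), and use all randomised participants.

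**Worked case: 22 points, control 50%.**
- 300 completers: n = 150, 0.50 v 0.72, s0 = 0.0563, s1 = 0.0549, z = 2.00, power 0.977.
- 375 kept, m = 0.20: n = 187.5, 0.40 v 0.576, s0 = 0.0516, s1 = 0.0508, z = 1.47, power 0.930.
- 375 kept, m = 0.36: 0.32 v 0.461, s0 = 0.0504, s1 = 0.0499, z = 0.84, power 0.800.

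**Power at control 40% / 50% / 60%**

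| Effect, randomised | Completers only (80%) | m = 0.10 | m = 0.20 | m = 0.36 |
|---|---|---|---|---|
| 22 points, 375 | 0.971 / 0.977 / 0.989 | 0.973 / 0.973 / 0.981 | 0.937 / 0.930 / 0.934 | 0.831 / 0.800 / 0.784 |
| 22 points, 225 | 0.845 / 0.863 / 0.909 | 0.851 / 0.852 / 0.876 | 0.770 / 0.755 / 0.763 | 0.616 / 0.582 / 0.565 |
| OR 1.57, 375 | 0.491 / 0.489 / 0.457 | 0.506 / 0.489 / 0.438 | 0.433 / 0.408 / 0.352 | 0.329 / 0.300 / 0.248 |

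**Direction.** Information is proportional to n(q-p)^2 / (r(1-r)). Relative to 80% completers, the failure-coded analysis at m = 0.20 carries about (1-r)/(1-0.8r) of the information. For 0.50 v 0.72, r = 0.61, so the ratio is 0.39/0.512 = 0.76. It is below 1 for any r, so with equal missingness of 20% or more the primary test is always the weaker one. At m = 0.10 the ratio is (0.9/0.8)(1-r)/(1-0.9r), which can fall on either side of 1. That is why the 10% column shows little change.

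OR 1.57 has power below 0.50 at 300 even with complete data. That shortfall is a separate matter. So is the stated 97 per group, which this formula does not reproduce from 22 points at 0.80 power (at most 80 per group are needed).

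**The case against.** Several points on the other side have force.

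- **Missed visits are not missing viral loads.** The 20% attrition and 80% retention figures are bounds on study follow-up. The primary outcome comes from the chart, in current patients of the clinic, with a laboratory draw as back-up ({18a}). Missingness of 10% or less is possible, and the loss is then small. This stands, and it is why a range is needed.
- **The dilution assumes that missing participants would have been suppressed as often as observed ones.** If 22 points is instead the effect in everyone, and missing participants would be suppressed at half the average rate, the dilution factor at 20% missing is 1 - 0.5 x 0.20 = 0.90. That is the 10% column, with almost no loss. This is a fair sensitivity case, but it redefines the effect that the sample-size section applies to the 300 analysed.
- **The cited 22-point effect may already count missing as failure.** The protocol does not say. If it does, no further dilution is due and power at 375 is about 0.99.
- **Missingness may differ by arm.** Reminders reach the arms by different routes ({18a}). At control 50%, with 20% missing in control, 22 points and 375 randomised, power is 0.986 with 15% missing in the intervention arm and 0.777 with 25%. A gain of that kind would partly reflect completeness rather than suppression.

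A reader might infer that the trial is badly underpowered at 375, that up to 40% of outcomes will be missing, or that the sensitivity analysis will hold a fixed 225-300 complete pairs. The document supports none of these. For 22 points at 375 with 20% missing, power stays at about 0.93. A figure of 40% needs entirely different people to be missing at each visit. And the sensitivity analysis uses available data, where one detectable value already settles the composite.

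None of these points makes the sample-size section and the primary missing-data rule describe the same analysis.

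**Conclusion.** The mismatch holds: the claim of adequate power at 225 to 375 is sized for the available-data sensitivity analysis, not for the primary test. On the protocol's 22-point effect, the consequence at 375 is modest with 20% of composites missing (a loss of about 3 to 6 points) and material with 36% missing (about 14 to 21 points, leaving power close to 0.80). At 225, even 20% missing brings power under the 0.80 that the section itself uses. For OR 1.57 at 375, power falls further, to 0.35-0.43 or 0.25-0.33, from a base that was already too low.

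These sizes rest on equal missingness by arm, control rates of 40-60%, and the planning effect holding among observed participants. The direction is secure under equal missingness of 20% or more. The size is not, because the protocol states neither the control rate nor the expected share of missing viral loads. Figure 3 is not available here, but the text applies attrition to N alone.

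**What to change.** Restate power for the analysis that is specified: all randomised participants, suppression at both visits, and a missing value counted as failure. Declare the assumed control-arm sustained-suppression rate, a range for the share missing at either visit (for example 10% to 36%), and whether the planning effect refers to observed or to all randomised participants. Show the result at both ends of 225 to 375, with one case of unequal missingness. Present about 300 as the approximate size of the available-data sensitivity analysis only.

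The cost is a short recalculation and possibly a less favourable power statement, mainly at the lower end of the range. No change to enrolment or data collection is needed.

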## Objectives {7}

The primary goal of this RCT is to evaluate the efficacy of the PATH intervention compared to usual care in a community-based HIV care setting on our pre-defined primary and secondary outcomes. Specific aims are threefold: (1) examine efficacy of PATH on primary (viral suppression at 6 and 12 months) and secondary outcomes (retention in HIV care; gaps in HIV medical visits; self-reported ART adherence); (2) examine the theory-informed mediators (e.g., increased self-efficacy to engage in HIV care, and reduced medical mistrust and HIV stigma), through which PATH may have the greatest impact on outcomes among Hispanic and Black PLWH; and (3) among those using substances, explore whether PATH significantly affects substance-related outcomes, including frequency of substance use and engagement in substance use treatment, when compared to usual care (UC). A sub-aim of the trial is to explore subgroup differences in efficacy based on factors such as race/ethnicity and substance use.

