## Assignment of interventions: allocation

### Sequence generation {16a}

Enrolled participants are randomized on a 1:1 basis into the PATH intervention or usual care. Randomization is determined using an online generated randomization schedule determined prior to the study launch (a priori). Randomization is not stratified by substance use or race, although recruitment efforts are made to help ensure that at least a third of the sample are people with active substance use (defined as using non-prescription stimulants or opioids in the past 6 months) and that the sample is representative of the HIV patient population at the community-based FQHC (i.e., at least 60% Hispanic).

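### The sample-size section claims adequate power for all the trial's aims, but its calculations cover only viral suppression in the full sample, not the exploratory Aim 3 among substance users

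*Protocol article*

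**What the plan says.** Sample size {14} gives two calculations. The first takes odds ratios of 1.57 (from a meta-analysis on viral load suppression), 1.68 and 3.47 (conventional small and medium sizes) and reports that the n for "adequate power of at least 0.85 ranges from" 179 to 204, or 263 to 339 with covariates. The second takes a peer navigation trial that "found a 22% difference-in-difference between the intervention and control arm on viral suppression over a 12-month follow-up" and, "assuming 0.80 power, alpha = 0.05, and 1:1 allocation ratio between intervention and control arms", arrives at 97 per group (194 in total). The section then concludes, "based on up to 20% anticipated attrition", that "a sample size between 225 and 375 would provide us with adequate power to achieve our aims". The goal is up to 375 randomised and about 300 analysed.

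Objectives {7} lists three specific aims. The third is, "among those using substances, explore whether PATH significantly affects substance-related outcomes, including frequency of substance use and engagement in substance use treatment", compared with usual care. The section on additional analyses {20b} again uses the language of exploration, but also calls the substance analyses one of the study objectives. It names frequency of use, cravings, sex acts in the context of substance use, and engagement in treatment.

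The only numerical target for substance users is in Sequence generation {16a}: recruitment efforts should help ensure that "at least a third of the sample are people with active substance use". Randomisation is not stratified by substance use.

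**The concern.** Read literally, the adequacy claim covers all three aims. The two observed effects behind it (odds ratio 1.57 and 22 points) are for viral suppression, and no calculation is done for a subset. Aim 3 can use only the substance users, and the recruitment floor guarantees far fewer of them than any sample size the section calls adequate.

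What is at stake is how Aim 3 results are read. Both the objective and the analysis section ask whether PATH significantly affects substance outcomes, and several outcomes are examined. A reader told that the trial is powered for its aims could take a non-significant result from 30 to 50 per arm as evidence of no effect, which samples of that size would not support.

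**Working it through.** **Inputs.** 225 to 375 randomised, 20% attrition, alpha 0.05, 1:1 allocation, and effects of 22 points and odds ratios 1.57, 1.68 and 3.47 (all Sample size {14}); substance-user share at least 1/3 (Sequence generation {16a}). *Assumed, because the protocol does not give them:* two-sided test, control rate 30–50%, one binary outcome at one time point, and the recruitment target's definition of active use (non-prescription stimulants or opioids in the past 6 months) as the Aim 3 population.

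**1. The plan's own figures.** Attrition reproduces: 300/0.8 = 375 and 179/0.8 ≈ 224. With the pooled two-proportion formula at 0.80 power, 97 per group follows from 40% vs 60% (20 points). A 22-point difference needs at most 80 per group (39% vs 61%). The 179–204 range does not reproduce for the small odds ratios: at 0.85 power, 1.57 needs at least about 716 in total and 1.68 about 540, over control rates of 10–70%; 3.47 needs about 98 to 172. This limits what the fix can say about the primary outcome.

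**2. Numbers guaranteed for Aim 3.**
- 225 × 1/3 = 75 randomised; × 0.8 = 60 analysed (30 per arm)
- 375 × 1/3 = 125 randomised; × 0.8 = 100 analysed (50 per arm)

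**3. Power at those numbers.** Power = Φ{(d·√n − 1.96·√[2p̄(1−p̄)]) / √[p₁(1−p₁) + p₂(1−p₂)]}, with n per arm, d = p₂ − p₁ and p̄ the mean rate.

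| Effect borrowed from the plan | 30 per arm | 50 per arm |
|---|---|---|
| 22 points | 0.40–0.41 | 0.60–0.62 |
| OR 1.68 | 0.16–0.17 | 0.23–0.25 |
| OR 1.57 | 0.13–0.14 | 0.19–0.20 |
| OR 3.47 | 0.61–0.65 | 0.83–0.86 |

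Example, 39% vs 61% with 50 per arm: (0.22 × 7.071 − 1.96 × 0.7071) / 0.6898 = 0.246, and Φ(0.246) = 0.60.

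**4. Detectable at 80% power, one time point.** For a binary outcome centred on 50%, about 35 points with 30 per arm and 28 points with 50. For a continuous outcome, 2.80 × √(2/n) gives 0.72 SD and 0.56 SD.

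**5. Share that would be enough.** For 22 points at 0.80 power, 160 analysed are needed: 160/300 = 53% of the sample at 375 randomised, or 160/180 = 89% at 225.

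**6. Where the claim holds for the primary outcome.** With 90 to 150 analysed per arm and effects centred on 50%, power is 0.85 to 0.97 for 22 points and 0.77 to 0.94 for 20 points. Twenty points reaches 0.80 from about 194/0.8 = 243 randomised. For odds ratios 1.57–1.68, power at 150 per arm is only about 0.46–0.61 for control rates of 30–50%, and falls to 0.40 at a 70% control rate with OR 1.57.

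**The case against.** Aim 3 is worded as exploration in both places where it appears, and an exploratory aim needs no power. The context of the section also makes it fairly plain that viral suppression was what was powered. This stands: low power for Aim 3 is not a design fault. What remains is an adequacy claim with no limit on its scope.

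A reader might infer that the plan fixes substance users at one third, so that 60 to 100 is the planned size. The documents do not support that. The target is a minimum, and recent stimulant or opioid use is itself an entry route under Eligibility criteria {10}, so the share may be higher. Objectives {7} also does not tie its substance-using group to the definition used for the recruitment target.

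A reader might also put a single figure on the shortfall, such as 20 to 45 points of power. That depends on applying a viral-suppression effect of 20–22 points to substance outcomes, for which the plan gives no effect. Across the plan's own effects at the floor numbers, the gap against 0.80 runs from about 67 points (OR 1.57, 30 per arm) to none (OR 3.47, 50 per arm).

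Finally, the calculation above compares one time point, whereas the statistical methods plan mixed models over repeated follow-ups, and several substance outcomes are not binary. This stands too. As an illustration, with an assumed within-person correlation of 0.5, averaging four follow-ups multiplies the variance by (1 + 3 × 0.5)/4 = 0.625, or by 0.625 − 0.25 = 0.375 with baseline adjustment. The 0.56 SD then becomes about 0.44 or 0.34 SD. The detectable effects must therefore be labelled as single-time-point figures.

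**Conclusion.** The point holds as a matter of scope. Nothing shown supports the adequacy claim for Aim 3, and the recruitment floor guarantees only 60 to 100 analysed substance users, against 179 for the smallest sample the section calls adequate. Under the stated assumptions power falls short of 0.80 for 22 points and for the small odds ratios at either end of the range. For OR 3.47 it falls short with 30 per arm but not with 50. These figures rest on borrowed effects, a single-time-point binary comparison and the minimum share of substance users; a higher share or repeated measures would improve them.

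The documents do not support the stronger conclusions that Aim 3 is badly designed, that it needs more participants, or that the investigators intend to read a null result as no effect. This is a minor correction of wording.

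**What to change.** In Sample size {14}:

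- Limit the adequacy statement to the primary outcome at the effect for which it holds, about 20–22 points: 22 points across 225–375 randomised, 20 points from about 243. Do not extend it to odds ratios of 1.57–1.68. Say primary outcome rather than Aim 1, because Aim 1 also includes the secondary outcomes.
- State that Aim 3 is exploratory and not powered, with at least about 60 to 100 analysed substance users expected. Give the detectable effect at 80% power for a single-time-point comparison (about 28–35 points, or 0.56–0.72 SD), and note that it is smaller if repeated measures are used.
- State that Aim 3 will be reported as estimates with confidence intervals, and that a non-significant result will not be read as no effect.

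The cost is a few sentences and a narrower power claim. No participants, visits or measurements are added.
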